**Figure 1 F1:**
[figure not shown]
**Flow-Chart acc. to CONSORT**.

### Randomisation and blinding

Randomisation is designed in a way that both treatment arms will have the same number of patients, with a randomisation ratio of 1:1 providing equal probability of assignment to each of the two treatment arms. Randomisation is stratified by clinical trial centre and will be performed as block randomization. A separate randomisation list will be created for each clinical trial centre using the Software RandList of the DatInf GmbH, Tübingen, Germany.

Only if a patient fulfils all eligibility criteria he/she will be randomised to an investigational treatment. This will take place during surgery, since part of the exclusion criteria can only be checked during the operation (liver resection). For allocation of the randomisation numbers to eligible trial participants each clinical trial centre will be provided with a set of identical look, opaque and well sealed envelopes. If a patient turns out to be eligible the investigator opens the next envelope in sequence. Inside he will find the randomisation number and the allocated investigational treatment. The sequence of opening the envelopes will be monitored regularly.

This is a single blinded clinical trial. The clinical trial patients will not be informed about their assignment to a study group. The randomization takes place in the operating room immediately before the application of the product. Thus the investigator does not know which product will be used during transection, during primary haemostasis, and when assessing the intra-operative inclusion criteria. However, the appearance of the products precludes a complete blinding of the investigators.

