**Methods/Design:**

This is a multi-centre, patient-blinded, intra-operatively randomised controlled trial. A total of 126 patients planned for an elective liver resection will be enrolled in eight surgical centres. The primary objective of this study is to show the non-inferiority of Sangustop^® ^versus a carrier-bound fibrin sealant (Tachosil^®^) in achieving haemostasis after hepatic resection. The surgical intervention is standardised with regard to devices and techniques used for resection and primary haemostasis. Patients will be followed-up for three months for complications and adverse events.

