### Statistical analysis

#### Primary Variable

The proportion of patients with haemostasis 3 minutes after application of the haemostat product as well as associated 95% confidence intervals will be reported for each treatment arm. The study null hypothesis is that Tachosil^® ^is more effective than Sangustop^®^. Non-inferiority will be demonstrated if the lower limit of the observed two-sided 95% confidence interval of the observed difference in proportions of Treatment Arm 1 - Treatment Arm 2 does not fall below -0.100. The analysis will be based on the per-protocol population and repeated for the intent-to-treat population. The intent-to-treat population consists of all consenting patients randomized into the study. The safety population comprises all treated patients. The Per-Protocol population excludes all patients who violated inclusion or exclusion criteria of the protocol.

If the 95% confidence interval for the treatment effect not only lies entirely above -0.1 but also above zero then there is evidence of superiority in terms of statistical significance at the 5% level. The difference in proportions between the two treatment arms (Treatment Arm 1 versus Treatment Arm 2) will be tested with a Fisher's exact test to reject the null hypothesis of no difference.

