#### Secondary Variables

The proportion of patients with haemostasis 5 minutes and 10 minutes after application will be reported descriptively based on intent-to-treat population as well as the per-protocol population. This will include the proportions, the estimated difference in proportions and the associated 95% confidence intervals. Differences in time to haemostasis will be tested with a log-rank test at the 5% alpha level. Kaplan Meier curves will be displayed, with median estimates and confidence limits provided. The analyses will be based on the intent-to-treat population and repeated for the per-protocol population.

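### Randomisation is stratified by centre, but no named analysis uses centre: a modest loss of efficiency, not a threat to validity

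*Protocol article*

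**What the plan says.** Under Randomisation and blinding the protocol article states "Randomisation is stratified by clinical trial centre and will be performed as block randomization". Each centre has its own list, and allocation is 1:1. The abstract gives the scale: "A total of 126 patients planned for an elective liver resection will be enrolled in eight surgical centres", which is about 15 to 16 patients per centre on average.

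The analysis sections do not return to centre:

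- **Primary interval.** Under Primary Variable, non-inferiority rests on a two-sided 95% interval for "the observed difference in proportions of Treatment Arm 1 - Treatment Arm 2", whose lower end must stay at or above the margin of -0.100. No interval method or strata are given there. The only interval method named anywhere is Newcombe-Wilson, under Sample size, in its two-sample form.
- **Superiority.** The difference in proportions "will be tested with a Fisher's exact test to reject the null hypothesis of no difference".
- **Time to haemostasis.** Under Secondary Variables: "Differences in time to haemostasis will be tested with a log-rank test at the 5% alpha level". Strata are not mentioned.

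**The concern.** Blocking within centre balances the arms in each centre, so differences between centres drop out of the treatment contrast. A pooled two-sample analysis still counts those differences as noise. Its interval is then wider than the design requires and its tests are conservative.

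Centre differences are plausible here. The Surgery section allows five resection techniques and requires surgeons to have done only 10 liver resections. The Discussion concedes that the observer cannot be blinded and that the reading of haemostasis is subjective, so the threshold for calling haemostasis may vary by site.

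What is at stake is some precision in the primary interval and some power in the superiority test. Settling the choice in advance also prevents a later selection between pooled and stratified results in a trial with unblinded observers.

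**Working it through.** **Inputs from the article.** 60 per arm; margin -0.10; one-sided 97.5% limit; 0.88 v 0.73 for non-inferiority; 0.93 v 0.73 for superiority; eight centres.

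**Assumptions, not in the article.** Between-centre SD on the logit scale of 0, 0.5 or 1.0. At 1.0, centres one SD either side of the mean have control rates of 0.55 and 0.90. The simulation in step 3 uses blocks of 4.

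**1. The plan's own figures.**
- Non-inferiority: exact enumeration of the Newcombe-Wilson lower limit gives 94.1% power, against the stated 93%. The plan used 100 simulations, whose Monte Carlo SE is about 2.6 points, so the figure reproduces.
- Superiority: the chi-square approximation gives 83.9%, against the stated 83%.

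**2. Primary interval, large-sample.**

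Pooled: SE_pool = sqrt(0.88 x 0.12/60 + 0.73 x 0.27/60) = sqrt(0.00176 + 0.003285) = 0.0710. Half-width = 1.96 x 0.0710 = 0.139.

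Stratified: replace p(1-p) in each arm by its average within centres, holding the overall rates at 0.88 and 0.73. This gives SE_str.

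- Stratified power = Phi(0.25/SE_str - 1.96), where 0.25 = 0.15 + 0.10.
- Pooled power = Phi((0.25 - 1.96 SE_pool)/SE_str), because the blocked difference truly varies with SE_str.
- Pooled one-sided error = Phi(-1.96 SE_pool/SE_str).

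| Logit SD | Stratified half-width | Narrower by | Pooled power | Stratified power | Pooled one-sided error |
|---|---|---|---|---|---|
| 0 | 0.1392 | 0% | 94.1% | 94.1% | 2.5% |
| 0.5 | 0.1365 | 2.0% | 94.4% | 94.9% | 2.3% |
| 1.0 | 0.1295 | 7.0% | 95.3% | 96.6% | 1.8% |

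Check at SD 1.0: SE_str = 0.1295/1.96 = 0.0661. Stratified power = Phi(0.25/0.0661 - 1.96) = Phi(1.82) = 96.6%. Pooled power = Phi((0.25 - 0.1392)/0.0661) = Phi(1.68) = 95.3%.

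**3. Primary interval, simulation.** 120 patients in eight equal centres, 40,000 trials per setting; pooled Newcombe against the Mantel-Haenszel risk difference with Sato variance.
- Power at SD 0, 0.5, 1.0: 93.9 v 94.1%, 94.4 v 95.0%, 95.0 v 96.5%. Unequal centre sizes give nearly the same.
- Part of the gain is the change of interval type. Against a pooled Wald interval (94.4, 94.9, 95.5%) the differences are -0.2, 0.1 and 1.0 points.
- One-sided error at the margin (0.63 v 0.73): pooled Newcombe 2.6, 2.6, 2.0%; Mantel-Haenszel with Sato variance 2.60, 2.85, 2.92%. The Monte Carlo SE is sqrt(0.025 x 0.975/40,000) = 0.08 points, so the Sato interval is slightly liberal once centres differ.

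**4. Superiority test at 0.93 v 0.73.** Exact power with no centre differences is 79.5% for Fisher and 85.4% for the uncorrected chi-square test. In simulation (eight centres of 15, split 7/8), Fisher stays at about 79% for SD 0, 0.5 and 1.0, while Cochran-Mantel-Haenszel has 86, 86 and 88%. Under equal rates of 0.73, Fisher's two-sided error is 2.9, 2.6 and 2.1%; Cochran-Mantel-Haenszel holds about 5%.

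At SD 0, therefore, 85.4 - 79.5 = 5.9 points of the gap of about 6 to 7 come from leaving Fisher, not from stratifying. The Cochran-Mantel-Haenszel figures are without continuity correction. A corrected chi-square test has 79.5% exact power, the same as Fisher.

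**The case against.** **Silence is not a statement.** This is a condensed article and the analysis plan is not shown. A reader might infer that every planned analysis ignores centre. The text supports that only for Fisher's test, and for the Newcombe-Wilson interval as used in the sample-size calculation. The primary interval and the log-rank test could be stratified in the analysis plan. This stands. What remains is that the tests and interval method the article does name do not follow the randomised strata.

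**Size.** A reader might infer that intervals are needlessly wide as a matter of fact, or that stratifying rescues a fragile non-inferiority test. Neither is supported. With no centre differences the interval gains nothing, and the article reports no between-centre spread. Larger power gains appear only with a rate such as 0.83 v 0.73, which the protocol does not plan, together with a very large spread (logit SD 1.5). At the planned rates power is already about 94%.

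**Validity.** A reader might also infer that the pooled analysis is unsound. It is not. Its error at the margin stays at about 2.5% or falls below it, which is the safe direction for a non-inferiority claim.

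**Fisher's role.** Fisher is an additional test, and the article also reads superiority from whether the interval lies above zero. Its low power matters to the extent that its p-value decides the claim.

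**Costs of stratifying.** Strata are small, only six of eight centres were recruiting at submission, and per-protocol exclusions can disturb balance within centre. These points stand and shape the remedy.

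**Conclusion.** The point holds as a modest improvement in efficiency. Centre is a randomisation stratum, the superiority test named cannot use it, and the other analyses do not mention it. For non-inferiority the benefit is small: an interval 0 to 7% narrower and at most about 1.5 points of power, over an assumed logit SD of 0 to 1.0. For superiority the benefit is larger, from about 79% to about 86 to 88%. With no centre differences that gain comes from leaving Fisher's test, and only the further rise to 88% at SD 1.0 reflects centre. Fisher also falls short of the 83% that the Sample size section promises for a different test. For the log-rank test no size can be given; the argument is one of direction only.

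**What to change.** Before the data are analysed, state the following:

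1. Base the primary difference on a Mantel-Haenszel-weighted risk difference stratified by centre, with a stratified score-type 95% interval (Newcombe or Miettinen-Nurminen), used for both the -0.10 and the zero comparison.
2. Replace Fisher's exact test with a centre-stratified Cochran-Mantel-Haenszel test without continuity correction.
3. Stratify the log-rank test by centre.
4. Fix a rule for pooling centres with very few patients, set without sight of outcomes by arm.
5. Keep the pooled analysis as a sensitivity analysis.

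The cost is analysis wording and no extra patients. The downside is the need for a small-centre rule. A Sato-variance interval can also run slightly liberal when centres are sparse and very different: about 3% one-sided at logit SD 1.0, and about 3.5% at 1.5. This is why a score-type interval is preferred. It was not itself simulated here, so its error at the margin should be checked at the expected centre sizes before it is adopted. If the analysis plan already specifies stratified methods, the article's Fisher test should be reconciled with it.

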### Statistical analysis

#### Primary Variable

The proportion of patients with haemostasis 3 minutes after application of the haemostat product as well as associated 95% confidence intervals will be reported for each treatment arm. The study null hypothesis is that Tachosil^® ^is more effective than Sangustop^®^. Non-inferiority will be demonstrated if the lower limit of the observed two-sided 95% confidence interval of the observed difference in proportions of Treatment Arm 1 - Treatment Arm 2 does not fall below -0.100. The analysis will be based on the per-protocol population and repeated for the intent-to-treat population. The intent-to-treat population consists of all consenting patients randomized into the study. The safety population comprises all treated patients. The Per-Protocol population excludes all patients who violated inclusion or exclusion criteria of the protocol.

If the 95% confidence interval for the treatment effect not only lies entirely above -0.1 but also above zero then there is evidence of superiority in terms of statistical significance at the 5% level. The difference in proportions between the two treatment arms (Treatment Arm 1 versus Treatment Arm 2) will be tested with a Fisher's exact test to reject the null hypothesis of no difference.

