### Sample size

The sample size was calculated to test for non-inferiority of Treatment Arm 1 (Sangustop^®^) versus Treatment Arm 2 (Tachosil^®^) in terms of haemostasis 3 minutes after application of the haemostatic product. The proportion of patients with a complete haemostasis 3 minutes after application will be assessed. In a previous study [4] the proportion of patients with complete blood clotting after 3 minutes for Tachosil^® ^was estimated to be 73%.

With 60 subjects in each group, the lower limit of the observed one-sided 97,5% confidence interval will be expected to exceed -0,100 with 93% power when the proportion of Treatment Arm 2, π_S_, is 0,730 and the expected proportion of Treatment Arm 1, π_T_, is 0,880; results are based on 100 simulations using the Newcombe-Wilson score method to construct the confidence interval [7].

In case of non-inferiority an additional two group χ^2^-test with a 0,050 two-sided significance level will have 83% power to detect the difference between an Treatment Arm 2 proportion, π_1_, of 0,730 and an Treatment Arm 1 proportion, π_2_, of 0,930 (odds ratio of 4,914) when the sample size in each group is 60.

Assuming a drop-out rate of 5% a total number of 126 patients needs to be enrolled. Figure 1 shows a flow diagram of the progress through the trial phases.

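### The add-on superiority claim has two unranked criteria, and its stated 83% power belongs to a chi-square test, not to the planned Fisher's exact test

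*Protocol article*

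**What the plan says.** The Protocol article describes the superiority step in two places.

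- **Sample size.** The step is conditional and additional: "In case of non-inferiority an additional two group" chi-square test "with a 0,050 two-sided significance level will have 83% power to detect the difference" between 0.730 in Treatment Arm 2 and a Treatment Arm 1 proportion "of 0,930 (odds ratio of 4,914) when the sample size in each group is 60". The control rate comes from the reference study, where "the proportion of patients with complete blood clotting after 3 minutes for Tachosil^® ^was estimated to be 73"%. The same section uses 0.880 for Treatment Arm 1 in the non-inferiority calculation, and names the Newcombe-Wilson score interval for that calculation.
- **Statistical analysis, Primary Variable.** If the 95% interval lies above the margin "but also above zero then there is evidence of superiority in terms of statistical significance at the 5% level". The next sentence says that the difference in proportions "will be tested with a Fisher's exact test to reject the null hypothesis of no difference". This section names no interval method and does not say how the two statements relate.

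**The concern.** One claim has three procedures attached to it: an interval criterion, Fisher's exact test, and the chi-square test on which the power rests. Fisher's test is more conservative than the other two. This has two consequences. The 83% describes a test that the analysis section does not plan. And some results would satisfy the interval criterion but not Fisher's test, with nothing in the text to settle the conclusion. The claim at stake is superiority over a product that the article calls a gold standard, on an endpoint that the Discussion describes as subjective and assessed without blinding. The rule should therefore be fixed in advance.

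**Working it through.** **Inputs.** Sample size section: n = 60 per arm; p2 = 0.73; p1 = 0.93 (superiority) and 0.88 (non-inferiority); two-sided alpha 0.05. Assumptions: Fisher's test is also run two-sided at 0.05, and the interval is Newcombe-Wilson, with and without continuity correction, because the analysis section names none.

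**1. Reproduce the 83%.** For the uncorrected chi-square test, power = Φ{[|p1 − p2|√n − 1.96√(2p̄(1 − p̄))] / √(p1(1 − p1) + p2(1 − p2))}, with p̄ = (0.93 + 0.73)/2 = 0.83.

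- 0.20 × √60 = 1.549
- 1.96 × √(2 × 0.83 × 0.17) = 1.96 × 0.5312 = 1.041
- √(0.0651 + 0.1971) = 0.5121
- (1.549 − 1.041)/0.5121 = 0.992, and Φ(0.992) = 0.839

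The odds ratio is (0.93/0.07)/(0.73/0.27) = 4.914, as printed. The 83% is therefore sound for the chi-square test.

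**2. Exact power of each rule.** All 61 × 61 outcome pairs were enumerated, each weighted by its binomial probabilities. The weights were summed over the pairs where the rule claims superiority of Treatment Arm 1.

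| Rule, 60 per arm | 0.93 v 0.73 | 0.88 v 0.73 |
|---|---|---|
| Uncorrected chi-square | 85.4% | 55.3% |
| Newcombe-Wilson 95% lower limit > 0, uncorrected | 85.2% | about 54% |
| Same, continuity-corrected | 80.9% | 48.4% |
| Fisher's exact, two-sided p ≤ 0.05 | 79.5% | 45.9% |

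Fisher is 83 − 79.5 = 3.5 points below the stated figure. It reaches 83% at about 65 per arm (64 gives 82.7%, 65 gives 83.5%).

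**3. How often the two criteria disagree** (interval above zero, Fisher not significant), from the same enumeration:

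| Interval | 0.93 v 0.73 | 0.88 v 0.73 |
|---|---|---|
| Newcombe-Wilson, continuity-corrected | 1.4% | 2.6% |
| Newcombe-Wilson, uncorrected | 5.7% | 8.3% |

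A Wald interval, which the article does not mention, would give 7.9% and 11.2%. The reverse conflict had probability 0.0% throughout.

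**4. Example tables.** The Newcombe-Wilson lower limit is d − √[(p̂1 − l1)² + (u2 − p̂2)²], where l and u are the Wilson limits for each arm. For 53/60 v 44/60, d = 0.150, l1 = 0.778 and u2 = 0.829. The lower limit is 0.150 − √[(0.883 − 0.778)² + (0.829 − 0.733)²] = 0.150 − 0.142 = +0.008.

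| Result | CI, uncorrected | CI, corrected | Fisher p | Chi-square p |
|---|---|---|---|---|
| 53/60 v 44/60 | +0.008 to +0.287 | −0.004 to +0.297 | 0.062 | 0.037 |
| 54/60 v 45/60 | +0.013 to +0.283 | +0.001 to +0.294 | 0.053 | 0.031 |
| 56/60 v 44/60 | +0.067 to +0.330 | +0.055 to +0.340 | 0.006 | 0.003 |

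The first row lies near the non-inferiority planning rates and conflicts only without the correction. The second conflicts with either version. The third lies near the superiority planning rates and does not conflict.

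**5. Wrong-direction error under equal rates.** The uncorrected Newcombe-Wilson rule claims superiority in 2.5%, 2.3% and 2.2% of trials at common rates 0.73, 0.80 and 0.88. Fisher does so in 1.5%, 1.4% and 1.2%.

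**The case against.** The best defence is that superiority is not what this trial is for. Non-inferiority is the sole primary objective, superiority is tested only after it, and the Discussion itself doubts that superiority would matter clinically. The analysis section can also be read as a sequence, in which the interval sentence explains what an interval above zero suggests and Fisher's is the formal test. On that reading the plan is conservative. The expected result under the superiority assumptions shows no conflict, and the size of any conflict depends on an interval version that a full protocol or analysis plan may fix.

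Most of this stands, and it limits the severity. It does not remove the point. The interval sentence asserts significance at the 5% level in its own right, so the sequential reading is possible but not stated. Naming the interval version would shrink the conflict but not end it, as 54/60 v 45/60 shows. And on the sequential reading, the printed power is still that of another test.

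A reader might infer more: that the 83% is a calculation error, that the trial is too small, that the false-positive risk is inflated, or that the sponsor would pick the favourable rule after seeing the data. The documents support none of these. The 83% is right for the chi-square test. The superiority power is reported at the 60 per group already given for non-inferiority. Both rules, as computed, hold the wrong-direction error at about 2.5% or less. The text is silent on precedence, which shows ambiguity and not intent.

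**Conclusion.** The point holds as an inconsistency of moderate to low severity. The superiority claim has two unranked criteria, and the 83% power does not belong to the planned Fisher's test, which has 79.5% at the same inputs. The chance that the interval claims superiority while Fisher does not reject is 1.4% to 5.7% at 0.93 v 0.73 and 2.6% to 8.3% at 0.88 v 0.73. These figures assume 60 evaluable patients per arm, independent binomial outcomes, a two-sided 5% Fisher test and a Newcombe-Wilson interval with or without continuity correction. The non-inferiority decision and the enrolment of 126 do not change.

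**What to change.** Before unblinding, name one governing superiority rule and make the power statement match it. Either choice is sound.

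- **Interval governs.** Superiority is claimed if the lower limit of the same two-sided 95% Newcombe-Wilson interval used for non-inferiority, without continuity correction, is above zero. The uncorrected chi-square p-value is reported as its companion, and the Fisher test is dropped. The interval and chi-square rules differ in only 0.2% of trials at 0.93 v 0.73 and 1.1% at 0.88 v 0.73, so the 83% stands approximately.
- **Fisher governs.** Restate the superiority power as about 79% at 60 per arm, and remove the statement that an interval above zero shows significance at the 5% level.

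The cost is a wording change in the protocol or analysis plan, with no extra patients or data. The first option keeps the printed power approximately valid. The second accepts about 3.5 points less power for a more conservative test.

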#### Secondary Variables

The proportion of patients with haemostasis 5 minutes and 10 minutes after application will be reported descriptively based on intent-to-treat population as well as the per-protocol population. This will include the proportions, the estimated difference in proportions and the associated 95% confidence intervals. Differences in time to haemostasis will be tested with a log-rank test at the 5% alpha level. Kaplan Meier curves will be displayed, with median estimates and confidence limits provided. The analyses will be based on the intent-to-treat population and repeated for the per-protocol population.

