### Interventions

#### Surgery

Liver resection (segmental or non-segmental) will be performed according to accepted surgical standards. Surgeons must be board certified and must have a minimum experience of 10 liver resections performed. A standardization of surgical technique will be done inasmuch as there is a restriction in the methods allowed for resection and for primary haemostasis.

The following techniques of liver resection are allowed:

▪ Cavitron Ultrasonic Aspiration (CUSA^®^)

▪ Hydrojet (pressurized jet of water)

▪ Clamp Crushing

▪ Scissors

▪ Stapler transsection

The following techniques of liver resection are not permitted:

▪ Argon beamer (Argon-Plasma Coagulation)

▪ Radiofrequency-assisted devices for parenchymal division (e.g. Habib™-Sealer, TissueLink™)

▪ Ultrasonic dissection (e.g. UltraCision^®^)

The following methods of primary haemostasis are allowed:

▪ Vascular clips

▪ Sutures

All other methods of primary haemostasis (e.g. Argon Laser, bipolar coagulation) are not permitted.

After primary haemostasis has been achieved and with persistent parenchymal bleeding the patient will be randomized to one of two treatment groups. Either Sangustop^® ^or Tachosil^® ^will be applied to the resection area according to the respective instructions for use and the time to haemostasis will be recorded.

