Some evidence from randomized controlled trials (RCT) exists regarding the use of fibrin sealants on their own or combined with a carrier material [2]. The efficacy of Tachosil^® ^which consists of a collagen fleece carrying the fibrin glue components human fibrinogen and human thrombin has been shown in many clinical studies in various indications and can be seen as a standard treatment superior to other locally applicable agents [4,5]. It was shown in a randomised controlled trial to be superior in obtaining intra-operative haemostasis over argon beamer in liver resection [4,10]. The study by Frilling et al. will serve as the reference for this study design and conduct. Participants, interventions and outcome measures are chosen to be similar or equivalent. Three study centres of the ESSCALIVER - Study (Graz, Heidelberg, München Grosshadern) participated in the reference study, too.

Patients undergoing elective hepatic resection are generally eligible for the study. Liver surgery is to be performed according to accepted surgical standards. For primary surgical haemostasis only sutures and clips are allowed.

The efficacy parameter is "time to haemostasis" which is assessed every minute as presence or absence of haemostasis. Different from the reference study the primary outcome measure is the proportion of patients who achieved haemostasis at 3 minutes. The reference study for Tachosil^® ^as well as the pre-clinical data for Sangustop^® ^suggest that at 3 minutes in the majority of cases (>70%) haemostasis will be achieved already. Thus the interesting "time to haemostasis" is the time between 1 and 3 minutes. However, the instructions for use for Tachosil^® ^require to press the device for at least 3 minutes to the wound surface, preventing a measurement before that time. Therefore, the proportion of patients with haemostasis after 3 minutes was chosen as the appropriate primary outcome. Patient proportions at other time points and the time to haemostasis (Kaplan Meier curves) will be assessed as secondary parameters.

A limitation of the study is that due to the nature of the products a blinding of the observer is not possible. Additionally, the assessment of the time to haemostasis is subjective and prone to bias. However, there is no better method available. This is reflected by the fact that it is the method of choice in comparable studies [2-6,10]."

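### If Sangustop is read before 3 minutes and Tachosil cannot be, the log-rank test on time to haemostasis is biased towards Sangustop; both arms need a common time grid

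*Protocol article*

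**What the plan says.** Three parts of the protocol article bear on this point.

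- **Statistical analysis, Secondary Variables.** "Differences in time to haemostasis will be tested with a log-rank test at the 5% alpha level". Kaplan-Meier curves with medians and confidence limits accompany the test. The 5- and 10-minute proportions are descriptive, so this is the only secondary efficacy endpoint with a planned hypothesis test.
- **Discussion.** Time to haemostasis is the efficacy parameter "which is assessed every minute as presence or absence of haemostasis", with no distinction between arms. The time of interest "is the time between 1 and 3 minutes". The Tachosil instructions, however, "require to press the device for at least 3 minutes to the wound surface, preventing a measurement before that time". The article draws one consequence: "Therefore, the proportion of patients with haemostasis after 3 minutes was chosen as the appropriate primary outcome". It then keeps time to haemostasis as a secondary parameter.
- **Interventions, Surgery.** Either product "will be applied to the resection area according to the respective instructions for use and the time to haemostasis will be recorded". The Sangustop instructions are not described, and no common first reading time is given.

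**The concern.** The article recognises that one arm cannot be observed in the window where it expects most events. It acts on this for the primary endpoint but not for the log-rank test. A Tachosil patient who is dry at 1 or 2 minutes can be recorded at 3 minutes at the earliest. If a Sangustop patient can be recorded at 1 or 2 minutes, two equally fast products yield different recorded times, and the difference always runs in favour of Sangustop. At the planning rate of 73% dry by 3 minutes, the recorded Tachosil median would be 3 minutes however fast the product really is.

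At stake is a nominally significant claim of faster haemostasis that reflects when each arm could be inspected. The Discussion expects differences of seconds to a few minutes, so a recording offset of 1 to 2 minutes is as large as the effect being studied.

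**Working it through.** **Inputs from the article.** Sample size section: 60 per arm; Tachosil proportion at 3 minutes 0.73. Discussion: one-minute grid; earliest Tachosil reading 3 minutes. Secondary Variables: log-rank at 5%, taken as two-sided.

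**Assumptions.** The first Sangustop reading is not stated, so it is varied over 1, 2 and 3 minutes. The split of early events over minutes 1 to 3 is not given, so four splits are used. Follow-up is censored at 10 minutes. The true time distribution is identical in both arms.

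**The plan's own figures first.** The article gives no operating characteristic for the log-rank test, but its planning figures reproduce closely:
- Non-inferiority power (0.88 v 0.73, margin -0.10, Newcombe-Wilson, 60 per arm): 94.1% by exact enumeration, against 93% stated from 100 simulations. The Monte Carlo standard error of the stated figure is √(0.93 × 0.07 / 100) = 2.6 points.
- χ² power (0.73 v 0.93): 83.9%, against 83% stated.
- Enrolment: 120 × 1.05 = 126, as stated.

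**Test statistic.** At minute k, let r be the number at risk (r₁ on Sangustop) and d the events (d₁ on Sangustop). Then Z = Σ(d₁ − d·r₁/r) / √ΣV, with V = d·(r₁/r)(1 − r₁/r)(r − d)/(r − 1). The test rejects if |Z| > 1.96.

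**Hand check with expected counts, constant hazard.** The hazard is −ln(0.27)/3 = 0.436 per minute, which gives event shares 0.354, 0.229 and 0.148 in minutes 1 to 3. Sangustop is read from minute 1. Tachosil events up to minute 3 are all recorded at minute 3.

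| Minute | At risk S / T | Events S / T | Expected S | O − E | V |
|---|---|---|---|---|---|
| 1 | 60.0 / 60.0 | 21.2 / 0 | 10.6 | +10.6 | 4.40 |
| 2 | 38.8 / 60.0 | 13.7 / 0 | 5.4 | +8.3 | 2.85 |
| 3 | 25.1 / 60.0 | 8.9 / 43.8 | 15.5 | −6.7 | 4.22 |
| 4–10 | 16.2 / 16.2 at start | equal | equal | 0 | 5.48 |

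The unrounded sum of O − E is 12.29 and the sum of V is 16.95, so Z ≈ 12.29 / √16.95 = 2.98. The chance of exceeding 1.96 is then about Φ(2.98 − 1.96) = 85%, although the products are identical.

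**Simulation, equal products (20,000 trials per cell, 60 per arm).** The split is of the 73% who are dry by 3 minutes. S and T mean significant in favour of Sangustop and Tachosil.

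| Split over minutes 1/2/3 | All patients dry before minute 3 | Sangustop from min 1: S / T | Sangustop from min 2: S | Both from min 3: S / T |
|---|---|---|---|---|
| Constant hazard | 58% | 85.4% / 0.0% | 79.0% | 2.5% / 2.7% |
| Even | 49% | 74.0% / 0.0% | 68.4% | 2.5% / 2.8% |
| 10/30/60 | 29% | 38.4% / <0.1% | 36.3% | 2.9% / 2.7% |
| 0/10/90 | 7% | 7.1% / 0.8% | 7.0% | 2.8% / 2.7% |

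Starting Sangustop at minute 2 removes little of the bias. A common start at minute 3 removes it: total rejection is 5.2% to 5.6%.

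**Sangustop truly worse (0.63 v 0.73 at 3 minutes, constant hazard).** With unequal first readings the test still favours Sangustop in 21% of trials and Tachosil in 0.1%. With both arms read from minute 3, it favours Sangustop in less than 0.1% and Tachosil in 29%.

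**The case against.** The strongest reply is that no sentence says Sangustop is read before 3 minutes. The Discussion gives a single schedule for both arms. Its argument (early window of interest, Tachosil unreadable there, hence the 3-minute endpoint) can be taken to mean that the early window was given up in both arms. On that reading there is no bias. First inspection times are also the kind of detail a full protocol may settle. This stands as a limit: a reader might infer that the test certainly favours Sangustop, and the article does not support that. It does not remove the point, because the article fixes an unrestricted log-rank test while stating a bar for one arm only.

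A second reply is that the size is assumed. That also stands. If few events fall before 3 minutes, rejection is barely above nominal (7.1% + 0.8%, about 8% in total). Only a range can be given.

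A third reply is that a required pressing time is part of using the product, so time to confirmed haemostasis under labelled use is a legitimate measure. In part this holds, and the difference would then not be wholly an artefact. But the Discussion describes the interest as haemostasis between 1 and 3 minutes, and nowhere says that the test is meant to capture a minimum set by the instructions.

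A reader might also infer that the primary result is compromised. It is not: the non-inferiority comparison, the Fisher test and the proportions at 3, 5 and 10 minutes do not depend on readings before 3 minutes through this mechanism. Nothing here supports changing how the 3-minute primary endpoint is counted.

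**Conclusion.** The concern holds conditionally. If Sangustop is read before 3 minutes, the log-rank test and the Kaplan-Meier medians are biased towards it. The direction follows from the article's own text. The size does not: with equal products, 73% dry by 3 minutes and 60 per arm, a nominal 5% test finds in favour of Sangustop in roughly 7% to 85% of trials, according to the assumed share of events before 3 minutes. If both arms are first read at 3 minutes, total rejection is about 5% and the problem disappears.

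This is a should-fix point. It touches one secondary endpoint, and the trial's main conclusion does not rest on it.

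**What to change.** Reconcile the Secondary Variables section with the Discussion, through the analysis alone:

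- State the first reading time in each arm.
- Code all haemostasis seen at or before 3 minutes as one category (≤3 min) in both arms.
- Run the log-rank test, or an interval-censored or discrete-time equivalent, and the Kaplan-Meier curves on that common grid.
- Report any earlier Sangustop readings descriptively, without a test.

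The use of either product does not change. The cost is that Sangustop readings at 1 and 2 minutes go untested, but they have no comparator. Where at least half of an arm is dry by 3 minutes, its median can only be reported as ≤3 min. If both arms are already first read at 3 minutes, nothing is lost.
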